
#### Data collection

Data are collected at three points – baseline, midline, and endline – through survey questionnaire, structured observation, along with stool and food sample collection (Fig. 3). At baseline (22 weeks of age), a short survey questionnaire is administered to the infant caregiver covering general household information, WASH access, infant health and animal contacts, with key details verified against the infant’s health card (e.g. date and place of birth, vaccination status). At the same time, a stool sample is collected from the infant for analysis (procedure described below). At midline (33 weeks of age) a second household visit is made with a structured observation of infant food preparation and feeding by the caregiver, and a second short questionnaire administered. Lastly, an endline visit is completed at age 37 weeks when a stool sample is collected and a third short questionnaire administered.

**Fig. 3 Fig3:**
[figure not shown]
Intervention and Data Collection Schedule

Intervention ‘fidelity’ is assessed using process evaluation methods [29] to collect qualitative and quantitative data through in-depth interviews, focus group discussions and structured questionnaires with CHVs and caregivers among a small sample of intervention and control clusters/households. At each follow-up point, any participant deaths are recorded along with the official cause of death.

All personal identifiers collected, including names and telephone numbers, will be stored separately from other, de-identified data. All data from the surveys, stool and environmental samples will be linked through a unique household code that cannot be traced back to an individual. GPS coordinates for individual households will recorded which represents identifying data that therefore requires careful protection. The GPS coordinates themselves, and the specific locations of households on maps, will not be published or presented with results of any analyses. All physical forms will be kept in a locked file cabinet in a locked office to prevent unintended release of information. All electronic data will be encrypted and stored on secured and password protected electronic databases.

#### Environmental and clinical sample collection

A stool sample is collected for each enrolled infant at baseline (22 weeks of age) and endline (37 weeks of age), and an infant food sample collected at midline (33 weeks of age) [Fig. 3]. For infant stool, the infant’s caregiver is given several unused, clean diapers and is asked to use the diapers on the child until they defecate. Once a child has defecated in a diaper, the caregiver folds the diaper so that the faeces is undisturbed on the interior and places the diaper in a provided biohazard bag. This procedure is used to prevent faeces samples from being collected off the ground (contaminated by soil) or from out of potties used by other children (contaminated by faeces). The bag is stored in a cool, dark, secure place until the research team returns to the household the next day and collects the sample. On the day of sample collection, the enumerator uses the scoop from the sterile collection bottle to scoop the stool from the diaper into the bottle, labelling the container with the date of collection and participant’s identification number. The bottle with the stool sample is placed in a bio hazard bag and the bag placed on ice in a cooler box and transported to the laboratory. At the laboratory, a lab technician sterilizes the outside of the bio hazard bag, removes the stool collection bottle from the bag, and records the sample as received. If the infant has not defecated on the day of sample collection or the stool sample is not sufficient for collection, the enumerator informs the parent or caregiver that they will return again the next day. This continues for up to 5 consecutive days.

For the infant food sample, the research team collects a sample of food cooked during the midline observation, and again several hours later after food has been used and stored for several hours. The caregiver is asked to place a sample of food in a sterile WhirlPak bag by the same means as she would feed a child (e.g. spoon, hands). Given that levels of contamination in food may increase with time during the day, time of collection is noted. Samples are labelled (date, time and study identification number), placed immediately into a cooler box, maintained at < 10 °C with ice packs, and then transported to the laboratory for analysis.

#### Laboratory analysis

Food samples are processed by enumerating a bacterial indicator of faecal contamination (*Enterococcus*). In brief, 1 ml (mL), 0.1 mL, and 0.01 mL dilutions of liquid foods are filtered through 0.45 μm pore-size membrane filter (Millipore Corp., Bedford, MA, USA), and the filters are cultured overnight on Slanetz &Barley Enterococcus Medium (OXOID CM0377). For solid foods, five grams are homogenized with 45 mL of sterile phosphate buffer saline (PBS), and 10 mL, 1 mL, and 0.1 mL dilutions are filtered and cultured on Enterococcus agar plates. Then the plates are incubated at 41 °C ± 0.5° for 24 h. After incubation, all light and dark red colonies are counted as *Enterococcus* and expressed as colony forming units (CFU) present per gram of food sample. A 10 ml volume of PBS used to resuspend solid food samples and wash membrane filters is processed each day as a food negative control.

A 200 mg sample of each stool sample is measured into a Zymo Shield Collection container and DNA and RNA is co-extracted using the ZymoBiomics DNA/RNA Mini kit according to the manufacture’s protocol (Zymo Corp., CA, USA). DNA/RNA is immediately stored in a − 20 °C freezer until transfer to the University of Iowa for molecular analysis. A second 200 mg stool sample is transferred to a labelled sterile Eppendorf tube and stored in a − 20 °C freezer as a repository in the event that primary samples are lost, mislabelled, or otherwise destroyed. All stools are processed in sterilized biosafety cabinets with laminar air flow, and one process negative control is prepared each day by leaving a Zymo Shield Tube open in the cabinet during stool processing, and then processing it for DNA/RNA extraction. Pathogen targets are detected and quantified by quantitative real-time polymerase chain reaction using Customized Taqman Array Cards on a ViiA7 thermocycler (Life Technologies, USA) as previously described with the exception of adding 300 uM bovine serum albumin (BSA) to reduce inhibition during PCR. Outcomes are defined as the pathogen-specific presence and concentration of individual pathogens, as well as the presence and diversity (sum of pathogen types) of all pathogens. Concentrations of individual pathogens per gram of stool are estimated by comparison of cycle thresholds of pathogen specific genes against standard curves for each reference of interest. In the event that pathogen genes are detected in process negative controls, monoplex PCR is used to verify that detection is true contamination. If negative controls are contaminated, the stool samples processed on the same day as the negative control are considered non-determined (ND) for the related pathogen.

#### Sample size calculation and analysis

Using a standard approach for calculating sample size for cluster Randomised Controlled Trials [30] we estimated the minimum detectable difference in primary and secondary health outcome measures with a planned total sample size of 750 children (375 intervention, 375 controls) across 50 clusters (25control/25 intervention) and with an anticipated intra-class correlation co-efficient (ICC) of 0.01. Our assumptions regarding baseline/control prevalence of any enteric infection and diarrhoeal disease are drawn from the most recent Multiple Indicator Cluster Survey (MICS) estimates for the prevalence of stunting and recent diarrhoea in Nyanza province [18], and the Demographic and Health Surveillance (DHS) survey national urban estimates for Kenya [31]; alongside, the national (Kenyan) and global estimates for prevalence of any enteric infection from the Global Enteric Multi-country Study (GEMS) [19]. In the absence of published effect size estimates for similar early childhood interventions on enteric infection prevalence and our assumption regarding effect size is cautiously estimated based on the effects on diarrhoea of different WASH interventions [32].

For the primary outcome, with 750 infants enrolled, and assuming a control prevalence of ≥1 of the 23 measured enteric infections of 0.7, and an intraclass correlation coefficient (ICC) of 0.01 we would have 80% power at a 5% level of significance to detect a minimum difference between arms in the prevalence of ≥1 infection of 11%. For our secondary outcome, with 750 infants, we would be able to detect a minimum difference in longitudinal prevalence of caregiver reported diarrhoea of 7% or greater, assuming a control longitudinal prevalence of diarrhoea of 15%.

The CONSORT Statement for cluster randomised controlled trials will guide the analysis and presentation of results [33]. To assess any imbalance between arms, descriptive statistics of demographic and outcome measures (where available) will be tabulated at baseline.

All analysis will be carried out on groups as randomised (‘intention to treat’). All analyses will account for the nature of the distribution of the relevant outcome and results will be presented as appropriate effects sizes at 95% confidence intervals. We account for clustering by using generalised estimating equations (GEE) and adjust for baseline differences in groups by including the cluster mean of our outcome at baseline as a covariate in statistical models. For all analyses, unadjusted and adjusted results will be presented, with covariates in adjusted analyses specified a priori.

#### Randomisation

Randomisation was undertaken remotely by the Clinical Trials Unit at the London School of Hygiene & Tropical Medicine (LSHTM). The unit of randomisation is the CHV catchment cluster, and, in discussion with the Ministry of Health for Kisumu County, the participating 50 clusters were selected from the 94 eligible clusters in the study neighbourhoods, with eligibility determined by the presence of an “active” CHV. The 50 active clusters were then randomly allocated 1:1 into two trial arms.

#### Blinding

This is a public health intervention seeking to change specific behaviours through direct engagement with participants such that blinding of participants to their allocation was not deemed possible. Randomisation of clusters was done remotely; enumerators, principal investigator, and trial statistician were blinded to allocation. The trial statistician will conduct final analyses blind to allocation.

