The intervention is delivered in four visits (Fig. 3) in collaboration between CHVs and specifically trained field staff. Visit 1 is a preliminary sensitization visit, led by participating CHVs in the weeks before children turn six months of age. During this first visit, CHVs reiterate existing messages regarding the importance of exclusive breastfeeding until 6 months of age, appropriate weaning foods, and their introduction after six months. The CHV also introduces new topics regarding food hygiene, including: environmental contamination, the risks associated with contaminated weaning food, and the potential health consequences - diarrhoeal disease, growth impairment, and cognitive deficits. The second visit is timed to coincide with children turning 6 months (25 weeks) old and introduces the “Happy Baby” aspect of the intervention. This household visit is designed to be a fun and lively experience for participating households and is led by specifically trained field staff who are accompanied by local CHVs. During this visit, field staff deliver a number of products designed to enable and trigger improved food hygiene practices, including: a baby bowl, a baby spoon, a baby cup, a handwashing container/station, a bottle dispenser of liquid soap (with instructions for self-refill), two deep and two rectangular sealable storage containers, and a branded “Happy Baby” feeding mat. In addition, intervention households receive a “Happy Baby” customised calendar with images that reinforce target behaviours and reference newly provided materials. Caregivers are instructed to record diarrhoea episodes on calendars between visits, ensuring that caretakers interact with and see messages. Visit 3 occurs when the child is 29 weeks old. This visit, once again lead by local CHVs, reinforces messages, discusses experiences with new target behaviours, and reviews new information on food hygiene. Visit 4 occurs when the child is 32 weeks old and introduces the “Successful Child” component of the intervention. Successful child images compliment “Happy Baby” materials by including images of older children in graduation gowns and caps. The successful child stage includes a “graduation event” for the caregiver, including a “food hygiene pledge”, and a forward-looking discussion about their aspirations for the infant and how to give their child a “Safe Start” in life. As an example of the materials, we include an image of the “Successful Girl” calendar given to caregivers in the intervention group (Additional file 1).

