#### Adverse events

The trial is monitored for adverse events and all reported adverse events are documented and reports are compiled on a quarterly basis. The principal investigators (JM and OC) will review any reported severe adverse events to assess the level of relatedness to intervention and take appropriate action.

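### The protocol claims enumerator blinding without limit, but it cannot hold at home visits made after the intervention kit is delivered at 25 weeks

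*Protocol article*

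**What the plan says.** The Blinding section concedes that "blinding of participants to their allocation was not deemed possible". It then says that randomisation was done remotely and that "enumerators, principal investigator, and trial statistician were blinded to allocation". It adds that the statistician's final analyses will be blind. No visit, task or outcome is excepted for enumerators.

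The Intervention description fixes when the arms become visibly different: "The second visit is timed to coincide with children turning 6 months (25 weeks) old". At that visit field staff hand over infant utensils, "a handwashing container/station, a bottle dispenser of liquid soap (with instructions for self-refill), two deep and two rectangular sealable storage containers" and a branded feeding mat. Intervention households also get a "customised calendar with images that reinforce target behaviours and reference newly provided materials", on which caregivers are told to note diarrhoea episodes.

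Data collection names three points: baseline (22 weeks), midline (33 weeks) and endline (37 weeks). At midline, "a second household visit is made with a structured observation of infant food preparation and feeding by the caregiver". Endline is a further visit with a stool sample and a questionnaire. The section on sample collection names the enumerator as the person who takes the stool at the household, returning for up to 5 consecutive days if needed.

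Under Adverse events, the principal investigators "review any reported severe adverse events to assess the level of relatedness to intervention".

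**The concern.** A data collector who enters a home where a branded mat, a custom calendar and a new handwashing station are in use can tell the arm, and so can one who finds none of these. The caregiver, who is not blinded, may also say so. An unlimited statement that enumerators were blinded does not fit these visits.

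What is at stake is the standing of the outcomes that depend on a person's observation or report: the food-hygiene practices watched at home, and the secondary outcome, days of caregiver-reported diarrhoea between 22 and 37 weeks. A reader who takes the Blinding section at its word would treat both as assessed by someone unaware of the arm. Detection bias in the observation, and reporting bias in the diarrhoea interview, would then be discounted when they should be weighed.

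**Working it through.** No sample size or power figure is involved. The check sets the blinding statement beside the schedule.

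**Timing** (Intervention description; Data collection)

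| Age | Event | Relative to kit |
|---|---|---|
| 22 weeks | Baseline questionnaire and stool | 25 − 22 = 3 weeks before |
| 25 weeks | Kit delivered, intervention homes only | – |
| 33 weeks | Home observation, questionnaire, food sample | 33 − 25 = 8 weeks after |
| 37 weeks | Endline questionnaire and stool | 37 − 25 = 12 weeks after |

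Two of the three data collection points fall after the kit.

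**Who is in the home.** The endline stool is collected by enumerators; this is explicit. The 33-week observer is not named: Data collection uses the passive, and the sample collection section speaks of the research team. That enumerators carry out the observation is therefore likely but inferred. The 37-week stool visit alone is enough to contradict the unlimited statement.

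**What could preserve blinding.** The article describes no step to keep the kit out of sight and no separate team for the observation. The observation is of food preparation and feeding, which is when the items are meant to be used.

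**Share of the diarrhoea window.** The window runs for 37 − 22 = 15 weeks, of which 37 − 25 = 12 weeks, or 12/15 = 80%, come after the kit (ignoring the one-week tolerances). Of the three data collection points, only midline and endline can capture diarrhoea that occurs after the baseline visit. If no other diarrhoea record is used, all of it is recorded after the kit is present.

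**Spill-over to later baseline visits.** Allocation is by cluster, recruitment is rolling, and planned size is 750/50 = 15 infants per cluster. The first scheduled visit at which a data collector could see a kit is 33 − 22 = 11 weeks after the first infant's baseline, or 37 − 22 = 15 weeks if enumerators attend only endline. Any infant enrolled in that cluster afterwards may be met by someone who already knows the arm. The number affected depends on recruitment pace and on whether the same enumerators return, neither of which is given. The range is 0 to 14 of the 15 infants in a cluster.

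**Roles where nothing conflicts.** No other section undercuts the statistician's blinding. The primary outcome is a laboratory qPCR result on stool, so what an enumerator sees in the home has little way to influence it.

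**The case against.** The strongest reply is that the sentence is in the past tense and follows directly on remote randomisation, so it may mean only that allocation was concealed when clusters were assigned. That reading is possible, but the sentence stands under Blinding, carries no limit, and will be read as covering outcome assessment. If concealment was meant, the wording should say so.

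A second reply is that a condensed article need not give every detail. That is true, but the point concerns a positive statement that other sections undercut. A fuller document could describe a separate observation team, but enumerators would still visit these homes at endline.

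Third, the main source of bias in reported diarrhoea is the unblinded caregiver, which the article already discloses and which would remain with perfectly blinded interviewers. This stands. Enumerator awareness is an additional source, and the protocol nowhere claims in so many words that diarrhoea or practices are blind-assessed; a reader would infer it.

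Several stronger readings are tempting and are not supported:

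- *That none of the stated blinding exists.* Nothing contradicts the statistician's blinding.
- *That the principal investigators must be unblinded because they assess relatedness.* Relatedness can be assessed from the event and its plausibility without knowing the arm, and the Adverse events section does not say that allocation is disclosed. The Blinding section refers to one principal investigator and the Adverse events section to more than one, so clarification is reasonable, but there is no contradiction.
- *That laboratory staff are unblinded because they are not listed.* This is an omission that a condensed article may make. Samples are labelled with study identification numbers, and nothing says that they carry the arm.
- *That confirmatory claims need to be moved to laboratory outcomes.* The primary outcome is already qPCR.

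**Conclusion.** The statement is wrong as written for one role and one period: enumerators at home visits after 25 weeks. It affects two of the three data collection points and, as planned, all 750 infants, since the absence of a kit is as informative as its presence. It may also affect some later baseline visits, in a number that the article does not allow one to fix. The outcomes concerned are observed food-hygiene practices and caregiver-reported diarrhoea; no size of bias can be derived from the document.

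The conclusion assumes that kits stay in the homes and in view, as the intervention intends, and that no masking step exists beyond what is described. For the observation itself it further assumes that the observer is an enumerator or another data collector entering the home; the endline visit does not need that assumption. The primary outcome, the sample size and the analysis are unaffected.

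**What to change.** Rewrite the Blinding section by role and stage:

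- The statistician is blinded, including for the final analysis.
- Enumerators are blinded at most until kits are present in the cluster, and not at the 33- and 37-week home visits.
- Observed food-hygiene practices, and caregiver-reported diarrhoea after 25 weeks, are not blind-assessed and are open to detection and reporting bias. The trial report should interpret them on that footing.
- State who carries out the 33-week observation.
- As a clarification only, say whether the principal investigators see allocation when assessing relatedness of severe adverse events.

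The cost is a few sentences. No additional staff, samples or visits are needed, and neither the sample size nor the analysis changes.

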#### Coordinating committees

The Trial Management Group includes representatives from each partner organisation (GLUK, Iowa University and LSHTM) chaired by the Principal Investigators (JM and OC). Modifications required to the protocol (intervention, participants, study design, analysis methods, or outcomes) during the study will be approved by the LSHTM Research Ethics Committee prior to implementation and the new information registered on the trial registry (clinicaltrials.gov). Need and frequency of audits for trials is independent of the investigators and is determined using a risk-based approach.

#### Adverse events

The trial is monitored for adverse events and all reported adverse events are documented and reports are compiled on a quarterly basis. The principal investigators (JM and OC) will review any reported severe adverse events to assess the level of relatedness to intervention and take appropriate action.

### Limitations

We had initially intended for the Safe Start intervention to be delivered exclusively by CHVs to demonstrate more directly the scalability of such an intervention within the existing health system structure and resource envelope. However, findings from our formative work demonstrated that such an approach would likely place undue burden on CHVs in the context of a research project. Although delivered by specialized field workers employed for the purposes of this study, our intervention is still considered to be deliverable within the CHV system and has been endorsed as such by the Ministry of Health for Kisumu County.

